The present study is planned with an aim to ascertain the effectiveness of a culturally appropriate nutritional education intervention delivered through health services to improve growth and complementary feeding of infants of age 6 to 12 months in Chandigarh; and to develop a child undernutrition tracking module for health workers to monitor child growth. The study design will be quasi-experimental. The study and control area will be selected purposively. The study will be conducted among vulnerable, migrant population usually belonging to lower/lower middle socioeconomic groups. The primary end point will be mean change in weight for age. The study population will be mother infant dyad with the age of infants between 4-6 months. Mother infant dyad will be enrolled at the baseline, and they will be followed up for 6 months after initiation of the intervention. Prior formative research in the form of focus group discussions will be conducted with mothers, health workers and community workers to explore culturally appropriate foods, affordability and knowledge regarding feeding practices. At the baseline, a pretested semi-structured questionnaire will be used to assess the knowledge and feeding practices of mothers and health workers. A baseline anthropometry of the infants will be done. During the intervention phase, both mothers and health workers will be trained as per modules of World Health Organization. The mothers will be provided nutritional education about culturally appropriate, easily available, and affordable low cost home based standard recipes that they will feed their children. The health workers will support mothers at individual level and do the growth monitoring of the children. A monthly work plan will be prepared for each health worker for monitoring growth of the infants. The resident will do supervision of health workers in the field every two months. At the end of the study, the same pretested semi-structured questionnaire and anthropometry will be used to find the improvement in feeding practices and growth respectively. The anthropometric data will be entered in excel sheet and z sores will be calculated. Statistical analysis will be done by using Statistical Package for Social Sciences version 16. Effectiveness of the intervention will be measured by calculating the difference in difference in mean change in weight between the intervention and control group.

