**Study design**

The study design will be quasi-experimental. The study and control area will be selected purposively. Study area will be Burail, an urbanized village in the catchment area of Civil Hospital, sector 45, Chandigarh. It is also one of the field practice area of department of Community Medicine, School of Public Health, PGIMER, Chandigarh. The population of Burail is 47,869 with 862 children below 1 year of age, as per annual health survey report, 2015-16. Most of the residents are migrants from neighboring states like UP, Bihar, Uttarakhand, Haryana and Himachal Pradesh, and belong to low or middle socio-economic groups. About 97% of children aged between 12 to 23 months in Burail are fully immunized, as per annual health survey report, 2015-16. Burail has 7 auxiliary nurse midwives (ANMs) and 19 anganwadi workers and centers. The control area will be Maloya, another urbanized village in Chandigarh. The background characteristics of control area are similar to study area in terms of vulnerability, migration of population, geographical location, socioeconomic status and baseline child health status. It has a population of 28,176 with 483children below 1 year of age as per annual health survey report 2015-16 of Civil Dispensary, Maloya. Maloya has 3 ANMs, 1 ASHA, 26 *anganwadi* workers and centers. About 90% of children aged 12-23 months are fully immunized in this area as per annual health survey 2015-16.

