**4. Post-intervention phase**

End line assessment of maternal knowledge of infant feeding and infant feeding practices, 24 hour dietary recall (consuming foods from 4 or more food groups, recommended number of meals and snacks per day) will be done by using the same pretested semi-structured questionnaire as was used in baseline assessment in study and control area (Annexure 2). The status of undernutrition will be assessed by anthropometry of the infant (wt/age, wt/length, length/age). Similarly, the knowledge of ANMs and *anganwadi* workers on infant feeding and status of growth monitoring will be checked by the same pretested semi-structured questionnaire (Annexure 3) in both intervention and control arm.

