**Secondary outcome:**

- Mean change in the weight for height.
- Mean change in the Height for age.
- Change in level of maternal knowledge and practice of recommended infant and child feeding practice following intervention.
- Change in proportion of infants who were consuming foods from four or more food groups
- Change in proportion of infants who were consuming the recommended number of meals and snacks per day

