**Statistical Analysis**

The data will be entered in Microsoft excel version 7. The data will be presented in frequencies, proportion and means. Statistical analysis will be done by using Statistical Package for Social Sciences version 16. T-test will be used to assess level of significance in difference between the means of the group. Chi square test will be done to assess significance of difference between proportions. Effectiveness will be measured by calculating the difference in difference in mean change in weight between the intervention and control group. Repeated measure ANOVA will be used to assess the difference in mean change in weight in the intervention group at baseline, 3 months and 6 months post intervention.

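### The categorical change outcomes get only a chi-square of proportions, while the difference-in-difference contrast is reserved for weight

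*Protocol*

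**What the plan says.** The Secondary outcome list words its categorical items as changes. One concerns the mothers: "Change in level of maternal knowledge and practice of recommended infant and child feeding practice following intervention". Another concerns the variety of the infants' diet: "Change in proportion of infants who were consuming foods from four or more food groups". A matching item covers the recommended number of meals and snacks.

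The data are paired. The Summary says "Mother infant dyad will be enrolled at the baseline, and they will be followed up for 6 months after initiation of the intervention". Under Post-intervention phase, the endline assessment "will be done by using the same pretested semi-structured questionnaire as was used in baseline assessment in study and control area".

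The arms are not randomised. Study design says "The study and control area will be selected purposively", with Burail as the study area and Maloya as the control.

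Statistical Analysis gives three relevant sentences. For means: "T-test will be used to assess level of significance in difference between the means of the group". For proportions: "Chi square test will be done to assess significance of difference between proportions". For the effect: "Effectiveness will be measured by calculating the difference in difference in mean change in weight between the intervention and control group". No sentence carries the last contrast over to a categorical outcome.

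**The concern.** For an outcome defined as a change, in a controlled before-and-after study, no intervention effect means equal change in the two arms. The plan recognises this for weight. For proportions, the natural use of the one test it names is intervention against control at endline, and the null of that test is equal endline levels. The two nulls coincide only if the arms start level, and purposive selection of one area per arm gives no assurance of that.

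Complementary feeding is half of the research question. If Burail mothers start with better knowledge, an endline chi-square can credit the intervention with that head start. If they start lower, it can miss a real gain. The baseline answers that would prevent both errors are already to be collected.

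**Working it through.** **Inputs from the protocol.** Two-sided 5% level (1.96) and 182 per arm, both from Sample size. The 182 does not follow from the formula printed beside it: (1.28 + 1.96)² × (0.65² + 0.65²) / 0.25² = 141.9. That is a separate matter; 182 is used here only because it is the planned number.

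**Assumptions, because the protocol gives no proportions.** Control arm 50% correct at baseline and 65% at endline. Intervention arm starts g points higher and also rises 15 points, so there is no effect. Within-mother correlation 0.3 or 0.5.

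**Endline chi-square with no effect.** With p₀ = 0.65, p₁ = 0.65 + g and p̄ their mean:
- SE₀ = √[2p̄(1 − p̄)/182]
- SE₁ = √[(p₀(1 − p₀) + p₁(1 − p₁))/182]
- rejection rate ≈ Φ[(g − 1.96 SE₀)/SE₁] plus the opposite tail

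| Baseline gap g | SE₀ | SE₁ | g/SE₀ | Rejects |
| --- | --- | --- | --- | --- |
| 0 | 0.0500 | 0.0500 | 0 | 5% |
| 5 points | 0.0491 | 0.0490 | 1.02 | 17% |
| 7 points | 0.0487 | 0.0486 | 1.44 | 30% |
| 10 points | 0.0480 | 0.0478 | 2.08 | 55% |
| 15 points | 0.0468 | 0.0461 | 3.20 | 90% |

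Simulation of paired binary answers (20,000 trials per case) agrees to within about one point.

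**Difference in change, same cases.** Its expected value is (0.65 + g − 0.50 − g) − (0.65 − 0.50) = 0 at every gap. In simulation it rejects about 5% throughout.

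**Other assumptions.** With a 40% control baseline and +20 points in both arms, the endline chi-square rejects 16.5%, 28%, 52% and 87% at gaps of 5, 7, 10 and 15 points.

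**Hidden effect.** Let control go from 50% to 60% and let the intervention arm gain 25 points, a true effect of 15. If the intervention arm starts 7 points lower, endline chi-square power is about 36%, against 70 to 83% for the difference in change. At 10 points lower it is about 16%, against 70 to 83%.

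**Cost when there is no gap.** Endline is 60% v 75%.
- Chi-square: SE₀ = 0.0491, SE₁ = 0.0485, power Φ[(0.15 − 1.96 × 0.0491)/0.0485] ≈ 87%.
- Difference in change: the variance of an individual change is b(1 − b) + e(1 − e) − 2ρ√[b(1 − b)e(1 − e)], for baseline b and endline e.
  - ρ = 0.3: 0.343 (control) and 0.308 (intervention), SE = √(0.651/182) = 0.0598, power Φ(0.15/0.0598 − 1.96) ≈ 71%.
  - ρ = 0.5: 0.245 and 0.221, SE = √(0.466/182) = 0.0506, power ≈ 84%.

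**Checks on candidate remedies, equal change and no effect.**
- ANCOVA with baseline as covariate rejected 19 to 55% of the time at baseline gaps of 0.2 to 0.3 SD (correlation 0.3 to 0.5). It does not test equal change when the arms start apart.
- An arm-by-visit term on the logit scale rejected about 9 to 10% at a 15-point gap, because equal change in points is not equal change in log odds.

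**The case against.** The chi-square sentence is generic: it names no outcome, visit or contrast. The maternal outcome is a change in level, so a score compared by t-test is open, and Annexure 2 has a field for a feeding score. A chi-square on the share of mothers who improved would come close to the right null. Contrast and pairing for secondary outcomes are often left to a statistical analysis plan. All of this limits the point. A reader might infer that the protocol assigns the chi-square to maternal knowledge, or that no use of a chi-square could address equal change; the text supports neither.

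A reader might also infer a baseline-against-endline chi-square within each arm, which would reject for any shared rise over six months and would treat paired answers as independent. The protocol does not describe that use. The only within-arm analysis it states is the repeated-measures ANOVA of weight.

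The feeding items raise a further difficulty. Infants enrol at 4 to 6 months, and the Current part of Feeding Practices in Annexure 2 skips ahead when the child is under 6 months and has breast milk alone or with other milk. Many current-feeding questions then have no baseline answer, so no individual change exists for them. Where few infants yet eat solids, there is also little room for a baseline gap. The problem therefore bites hardest on the knowledge items, which are asked of every mother at both visits.

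Finally, Study design describes the areas as similar, and no knowledge gap is documented. The 7-point case matches the 97% v 90% immunisation figures given there, but only as an illustrative size.

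What survives is that this is not mere silence. The protocol states a test for proportions and confines the change contrast to weight.

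**Conclusion.** The point holds in limited form. The analysis named for proportions does not, as written, match secondary outcomes defined as changes in the same dyads in non-randomised areas. Used between arms at endline, it turns a baseline gap into apparent effect or masks a true one.

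The direction follows from the nulls alone. The size rests on assumed levels, gains, gaps and correlations, and with level baselines the endline test is valid and more powerful. The primary weight analysis is not touched. This is worth correcting before analysis, but it affects secondary outcomes only.

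**What to change.** In Statistical Analysis:

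- State that for categorical change outcomes asked at both visits, the effect is the between-arm difference in change from baseline to endline, in percentage points. Test it by a t-test on the individual change, or by the arm-by-visit term in an identity-link GEE clustered on mother.
- If a knowledge or practice score is used, t-test the individual change. Do not offer ANCOVA as equivalent.
- For any within-arm description, use McNemar rather than chi-square.
- For current-feeding items skipped at baseline in infants under 6 months, where no baseline answer exists, report the endline between-arm comparison and say that it is not a change.

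The cost is a few sentences and a little more analysis, with no new data. If the areas turn out to start level, power is lower (about 71 to 84% against 87% in the illustration). The change does not remove the confounding from having one area per arm.

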**Ethical Issues**

The approval for the study will be taken from the Institutional Ethics committee of PGIMER, Chandigarh. A written informed consent will be obtained from parents of infants and AWW/ANMs prior to their recruitment in the study (Annexure 6). Participant information sheet (Annexure 7) will be provided to all the participants of the study. Confidentiality of study subjects will be maintained. The parent/legal guardian/ANM/AWW will be given the right to remove their child from the study or to withdraw consent to their participation in the study, at any time without reprisal.

**ANNEXURE 1**

**Focus Group Discussion Guide for Mothers/ Caregivers**

Title: Effectiveness of a culturally appropriate nutrition educational intervention delivered through health services to improve growth and complementary feeding of 6 months to 1 year old infants in Chandigarh: a quasi experimental study.

Name of institute: Post graduate institute of medical research and training (PGIMER)

Estimated time: 90 minutes at maximum

**Objectives:**

1. To explore current practice, barriers, facilitators on complementary feeding (CF) from perspectives of mothers/ ANMs

2. To explore the culturally appropriate foods and foods that is available to families in your area.

3. To explore the knowledge and attitude of mothers/ANM regarding complementary feeding.

4. To identify the role/influence of the family members, especially grandmother and husband on decision making of the mother to give appropriate complementary foods.

5. To identify potential communication channels for infant and young child feeding.

**Subjects:**

A group of 8-10 mothers/ caregivers / 3-4 ANMs/ 2-3 community representatives will be conveniently selected from the community. Age group difference, economic conditions (poor and non-poor) and different children groups (6-8 months and 9-11 months) will be considered to select purposive participants. In total, 2 FGDs with the participants will be done.

Materials: Pieces of colored paper, different colored pens, audio recorders/ video recorders.

**Methods:**

The focus group discussion will be facilitated by the researcher who is the junior resident and a note-taker. The discussion will be audio recorded/video-recorded if participants agree to do so. Free listing and ranking will be applied to identify the common benefits, disadvantages, roles of family members etc. The following topics will be explored:

- Culturally appropriate foods and foods that is available to families in your area.
- gap between knowledge and action of mothers
- frequency of feeding etc.

**FGD for mother included the following discussion points:**

1. At what age should the mother start to feed her child foods other than breastmilk? Why?
2. What are the current feeding practices of your child?
3. What are the culturally appropriate foods available in your area?
4. Can you tell us what foods are appropriate to give children 6-12 months? And why?

PROBE: any foods including 1) cereals (rice), 2) meat, fish, egg, 3) fruits (banana, mango), 4) vegetable (saag, tomato, gobi), 5) liquids like (tea, milk)

1. Is there any difference between what you would give to children 6-8 months old and what you would give to children 9-12 months old? (E.g.: daal ka pani for the former and khichadi, dalia for the latter)
2. What foods are NOT good/appropriate for children 6-12 months? And why? ( not good taste, take time to prepare, cook, feed the child…….)
3. What is the support you have to feed your child?

(PROBE: preparing, cooking, feeding the child, encourage the child to eat)

1. Who else in the family supports the mother to feed her child? (FREE LISTING then RANKING who is the most supportive (PROBE: the father, the grandfather, cousin, neighbour)

**FGD for health workers included the following discussion points:**

1. What are the factors that contribute to under nutrition among children in this community?
2. What are the current practices, barriers, facilitators and influencers complementary feeding (CF) in the community ?
3. At what age should the mother start to feed her child foods other than breastmilk? Why?
4. What are the culturally appropriate foods available in your area?
5. Can you tell us what foods are good / culturally appropriate to give children 6-12 months? And why?
6. Is there any difference between what you would give to children 6-8 months old and what you would give to children 9-12 months old?
7. What foods are NOT good/appropriate for children 6-12 months? And why?
8. How do you support the mother to feed her child? What more can you do to support the mother? FREE LISTING (PROBE: preparing, cooking, instructing, demonstrating the mother to feed the child, feeding the child, encourage the child to eat)
9. How can you improve the complementary feeding practices in the community?

Also, after an issue has been discussed, a summarization will be done to ensure that all opinions surrounding the issue have been covered.

**ANNEXURE 2**

**Questionnaire for mother-infant dyad**

Title: Effectiveness of a culturally appropriate nutrition educational intervention delivered through health services to improve growth and complementary feeding of 6 months to 1 year old infants in Chandigarh: a quasi experimental study.

**Institute: Department of Community Medicine, PGIMER**

**I. Basic information of mother/ caregiver:**

1. Unique ID no. …………………………
2. Name - ……………………………..
3. Age(years) - ………………………………
4. Sex: 1= M, 2=F
5. Address - ……………………………………………………..
6. Area: 1. Urban 2. Rural 3. Slum
7. Phone no. ……………………………….
8. Religion- 1. Hindu 2. Muslim 3. Sikh 4 Christian 5. Others.
9. Caste – 1.Gen 2. SC 3. ST 4. OBC 5. others
10. Education- 1/2/3/4/5/6/7
11. Occupation - 1/2/3/4/5
12. Monthly income of the mother:…………..
13. Marital status – 1/2/3/4/5/6
14. If mother is working who will take care of the baby ………….( 1 = in laws, 2 = crèche, 3 = others specify …………………. 4.By self )
15. Type of family- 1. Nuclear family 2. Joint family 3. Three generation family 4. Broken family 5. Other specify………

Family profile –

| Serial no. | Name | Age | Sex | Relationship with the head | Education | Occupation | Monthly income |
| --- | --- | --- | --- | --- | --- | --- | --- |
|  |  |  |  |  |  |  |  |
|  |  |  |  |  |  |  |  |
|  |  |  |  |  |  |  |  |
|  |  |  |  |  |  |  |  |
|  |  |  |  |  |  |  |  |
|  |  |  |  |  |  |  |  |
|  |  |  |  |  |  |  |  |

1. **Relation to family member-** self-1, father-2, mother-3, sister-4, brother-5, grand (father-mother)-6, uncle & aunt-7, other-8
2. **Gender-** Male- 1, Female*-* 2
3. **Education-** illiterate-1, primary school certificate- 2, middle school certificate - 3, High school certificate - 4, Intermediate or post high school diploma-5, Graduate or post graduate - 6, Professional or Honours- 7
4. **Occupation -** 1. Working (Govt./Private) 2. Homemaker 3.selfemployed
    4. Labourer/ maid 5. Student
5. **Marital status-** unmarried-1, married-2, widow-3, separated-4, divorce-5, married but not gauna-6
6. Total income of the family-…………..
7. Kuppuswamy SES score:……………
8. Socioeconomic status (According to modified Kuppuswamy Scale, 2014) – 1.Upper class 2. Upper middle class 3. Lower middle class 4. Upper lower class 5. Lower class
9. Food security score:………….(1= always enough food to eat, 2 = sometimes not enough food to eat, 3 = often not enough to eat)

**II. Child Information sheet**

1. Unique ID no of the child:
2. Name - …………………….
3. Father’s Name - ………………………….
4. D.O.B. - …………………(dd/mm/yy)
5. If date of birth not available age of the baby as per caregiver:………(dd/mm/yy)
6. Completed age at enrolment - …………..months …………days
7. Sex – ……….(1 = M 2 = F)
8. Was the child born at …………( 1= hospital, 2= home, 3=other)
9. Order of birth – 1 / 2 / 3 / 4 / 5 / 6 and above.
10. Birth weight (in Kg) - …………………….
11. Birth:………………(1= Term, 2= Preterm…….Weeks)
12. Immunization status –

| Sr. No. | Vaccine | date of administration of vaccine | age at which vaccine administered | Status- (1= Received/2=not received) |
| --- | --- | --- | --- | --- |
|  | Date of Birth |  |  |  |
| 32. | BCG |  |  |  |
| 33. | OPV-0 |  |  |  |
| 34. | Hep B -0 |  |  |  |
| 35. | DPT1/ Penta1 |  |  |  |
| 36. | DPT2/Penta2 |  |  |  |
| 37. | DPT3/Penta3 |  |  |  |
| 38. | IPV |  |  |  |
| 39. | Rotavirus vaccine |  |  |  |
| 40. | OPV-1 |  |  |  |
| 41. | OPV-2 |  |  |  |
| 42. | OPV-3 |  |  |  |
| 43. | Measles |  |  |  |
| 44. | Vitamin A |  |  |  |

45. Present weight (Kg) -…………………..

1. Present length(cm) - ………………..
2. Malnutrition status: ……………(1= Normal, 2= Moderate Malnutrition, 3= SAM)
3. Wt/age : ………..
4. Wt/ht : ………….
5. Ht/age: ………….

**III. Housing situation:**

1. Living in a rented accommodation: .…{1= Yes , 2 = No (own house), 3= (No, others…..)}
2. Type of house: …………(1=*kutcha*, 2 = *pucca,* 3 = *kutcha-pucca*)
3. No. of rooms ……..(1= 1 room, 2 = 2 rooms, 3 = 3 rooms, 4 = 4 rooms)
4. Overcrowding at home: …..(1= yes, 2 = no)
5. Safe water supply: ………. 1.yes 2.no
6. Main type of cooking fuel used : ……..1. LPG 2. Kerosene stove 3. *Chulha*
7. Sanitary latrine :……….1=yes, 2=no
8. If yes: 1= own toilet, 2 = shared toilet If yes: 1= own toilet, 2 = shared toilet

**IV. Maternal knowledge regarding breastfeeding and complementary feeding practices**

1. Which milk is best for the baby?

1.Breast milk 2.Formula milk 3.Animal milk 4. Don’t know

1. Up to which month exclusive breast feeding should be given?

1. Up to 6 months 2.4-6 months 3.7-8 months 4.Don’t know (998)

1. Can bottle feeding be given to baby? 1.Yes 2.No 3.Don’t know(998)
2. At what age complementary foods (solid, semisolid or soft foods) should be introduced? 1.4-6 months 2.At 6 months 3.7-8 months 4. Don’t know(998)}
3. Name three complementary foods that you think are good for a6-9 month old baby? ………………………………………………………………..(1.Know 2.Don’t Know(998))

(Note: If respondent answer any 3 food items then select option1.Eg: Khichidi, sujikheer, mashed fruits and vegetable, roti, mashed dhal, rice with dal, dhaliya with milk, basen or attacheera etc. If respondent say fruit juice, dhal water, milk then select option 2)

1. How many times a day solid/semi-solid foods should be given to 6-8 months baby? 1.= 3or more times 2. 1-2 times 3.Don’t know (998)
2. What should be the consistency of food given to baby? 1. Thick 2.Thin 3.Very thin
3. Name three snacks that can be given to a 6-8 month old baby? ……………………………………………………(1.Know 2.Don’t Know(998)) (Note: If respondent answer any 3 food items then select option1.Eg: fruits- banana, apple, papaya, mango,chiku,orangeetc, murmura, biscuits. If respondent say kurkure, chocolate, chips, fruity then select option 2)
4. What is the quantity of solid/semi-solid foods your child can consume at his/her age per feed?

| 1. 1-2 teapoonfuls | 1. 1/2 of a 250 ml cup |
| --- | --- |
| 1. 3-5 teapoonfuls | 1. 3/4^th^ of a 250 ml cup |
| 1. 2-3 tablespoonfuls | 1. Full cup |
| 1. 4-5 tablespoonfuls |  |

1. Can tea / sugar drinks/ coffee can be given to your child? 1.Yes 2. No
2. Should ghee or oil be used in complementary foods? 1.Yes 2. No 3.Don’t know (998)
3. Do you know till what age breastfeeding can be continued?
    1.Less than 1 year 2. 1 year - < 2 years 3.Upto& beyond 2 years 4. Don’t know (998)
4. Are commercial baby foods better for infants than homemade foods? 1.Yes 2.No 3.Don’t know (998)
5. Do you need to wash hands with soap and water before feeding the child? 1.yes 2. no
6. If your child is not taking food, should he/she be threatened or bribed?
    1. Yes 2. No 3. Sometimes

